**Methods:**

A 2-armed, single-blinded, parallel, and randomized controlled trial will be conducted with 58 parents or caregivers of children who attend the Clinics of Pediatric Dentistry at the Bauru School of Dentistry, considering an attrition of 10% and a significance level of 5%. The participants will be randomized into test and intervention groups, being respectively exposed to fluoride-related information and disinformation presented on a computer with simultaneous monitoring of their psychophysiological reactions, including analysis of their heart rates (HRs) and 7 facial features (mouth outer, mouth corner, eye area, eyebrow activity, face area, face motion, and facial center of mass). Then, participants will respond to questions about the utility and truthfulness of content, their emotional state after the experiment, eHealth literacy, oral health knowledge, and socioeconomic characteristics. The Shapiro-Wilk and Levene tests will be used to determine the normality and homogeneity of the data, which could lead to further statistical analyses for elucidating significant differences between groups, using parametric (Student *t* test) or nonparametric (Mann-Whitney *U* test) analyses. Moreover, multiple logistic regression models will be developed to evaluate the association of distinct variables with the psychophysiological aspects. Only factors with significant Wald statistics in the simple analysis will be included in the multiple models (*P*<.2). Furthermore, receiver operating characteristic curve analysis will be performed to determine the accuracy of the remote HR with respect to the measured HR. For all analyses, *P*<.05 will be considered significant.

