## Methods

### Trial Design

A 2-armed, single-blinded, parallel, and randomized controlled trial (trial registration number: U1111-1263-8227) will be conducted with 58 parents or caregivers of children who attend the Clinics of Pediatric Dentistry of the Bauru School of Dentistry, considering an attrition of 10% and a significance level of 5%. The participants will be randomized into test and intervention groups, being respectively exposed to fluoride-related information or disinformation presented on a computer, with simultaneous monitoring of their psychophysiological reactions, such as heart rate (HR) and 7 facial features (mouth outer, mouth corner, eye area, eyebrow activity, face area, face motion, and facial center of mass). Then, the participants will respond to questions about the utility and truthfulness of content, their emotional state after the experiment, eHealth literacy, oral health knowledge, and socioeconomic characteristics. The Shapiro-Wilk and Levene tests will be used to determine the normality and homogeneity of data, which could lead to further statistical analyses for elucidating significant differences between groups using parametric (Student *t* test) or nonparametric (Mann-Whitney *U* test) analyses. Moreover, multiple logistic regression models will be developed to evaluate the association of distinct variables with the psychophysiological aspects. Only factors with significant Wald statistics in the simple analysis will be included in the multiple models (*P*<.2). Furthermore, receiver operating characteristic (ROC) curve analysis will be performed to determine the accuracy of F_9_ (remote HR) concerning F_8_ (measured HR). For all analyses, *P*<.05 is considered significant.

This protocol is written according to the SPIRIT (Standard Protocol Items for Clinical Trials) guidelines. Figure 1 depicts the study design synthesis [21]. The peer review reports are available in Multimedia Appendices 1 and 2.

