#### Intervention

The experiments will be conducted based on the methodology described by Kirkwood and Minas [22]. After agreeing with the terms and signing the free consent form, the participants will be led to a silent room and will sit in front of a computer. At this moment, the researcher will instruct the participants about the test functioning (consumption of fluoride-related digital content), highlighting the presentation format and time and explaining the technical issues regarding the capture of psychophysiological reactions, besides encouraging them to persist until the end of the activity, and maintain the sitting posture during the process. To monitor the HR (1 Hz), the participants will be asked to wear 2 digital sports watches (Polar Ignite 2 and Polar Verity Sense) positioned at 7 cm away from their wrists. The HRs captured by Polar Ignite 2 will be used in the analyses, whereas the HRs captured by Polar Verity will be recorded as backup measurements.

Throughout the experiments, a camera (Canon Vixia HF R800 Full HD) will record the participants’ facial expressions. The camera will be placed on a tripod to remain slightly slanted upward and placed to face people at approximately 0.6 m. The video will be recorded in color at 60 frames per second (fps) with a resolution of 1920 × 1080 pixels and saved in the AVCHD-HD format. In addition, a spotlight will be positioned 1.6 m from participants and 45 cm above the camera level to avoid shadows on their faces during the recording. To standardize the recording of the videos, a white photographic background will be positioned approximately 60 cm behind the participants.

Initially, the psychophysiological reaction of participants will be monitored for 150 seconds while they watch a relaxing video with a classical music piece playing in the background (baseline). Next, the monitor will show 25 messages containing fluoride-related information (control) or disinformation (test) in a 6.25-minute slide presentation (15 seconds to read each message).

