### Data Collection, Management, and Analysis

First, the HR data of the participants will be exported from Polar Ignite 2 and Polar Verity Sense to Microsoft Excel (Microsoft Corporation) as.csv files. Further, the sociodemographic, oral health knowledge, self-perception about information, and eHEALS data will be manually entered into Excel sheets. Moreover, the videos will be exported from the camera and stored in a closed repository for further analysis, according to the findings of Bevilacqua et al [31,32]. Notably, the features were designed based on previous reports regarding the potential to distinguish participants' emotional states [31-34]. As a result, 9 psychophysiological features will be calculated, with 7 related to facial activity and 2 to HR, as summarized in Table 2.

**Table 2 table2:** Description of the psychophysiological characteristics to be measured in the clinical trial.

Feature number	Facial landmark	Description
F_1_	Mouth outer	Monitor the zygomatic muscle
F_2_	Mouth corner	Monitor the zygomatic muscle
F_3_	Eye area	Monitor the orbicularis oculi muscle (eg, blinking)
F_4_	Eyebrow activity	Monitor the corrugator muscle
F_5_	Face area	Monitor facial movement to and away from the camera
F_6_	Face motion	Describe the total distance the head has moved in any direction in a short period
F_7_	Facial COM^a^	Describe the overall movement of all 68 facial landmarks
F_8_	Measured HR^b^	Measurement of HR using Polar Ignite 2 and Polar Verity Sense
F_9_	Remote HR	Estimated measurement of HR using the rPPG^c^ technique

^a^COM: center of mass.

^b^HR: heart rate.

^c^rPPG: remote photoplethysmography.

Features F_1_ to F_7_ are grounded on 68 facial landmarks automatically detected using constrained local neural fields (CLNFs) and are calculated using the Euclidian distance between those facial landmarks [31,32]. However, subjects have unique facial shapes and characteristics, which could prevent their comparison. Thus, we will first calculate a normalization coefficient for the Euclidian distance between the upper and lowermost anchor landmarks to mitigate this problem [31]. Additionally, feature F_9_ is based on remote estimations of HR performed using the established remote photoplethysmography  (rPPG) technique [35]. This is an extremely resilient technique when estimating the HR under challenging conditions and could be combined with the disinformation consumption scenario.

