Statistical analysis will be performed using Stata 17.0 software (StataCorp LLC, College Station, TX, USA). The questionnaire and psychophysiological data will be expressed through descriptive analysis (mean, SD, median, minimum, maximum, and percentage of variation). Moreover, the Shapiro-Wilk and Levene tests will be performed to analyze the normality and homogeneity of data to determine significant differences between groups by the Student *t* test (parametric analysis) or Mann-Whitney *U* test (nonparametric analysis). Further, multiple logistic regression models will be developed to evaluate the association of distinct variables with the psychophysiological aspects. Only factors with significant Wald statistics in the simple analysis will be included in the multiple models (*P*<.2). Furthermore, ROC curve analysis will be performed to determine the accuracy of F_9_ concerning F_8_. For all analyses, *P*<.05 will be considered statistically significant.

It is noteworthy that anonymized data will be shared in a public repository after the end of this study.

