## Discussion

### Principal Findings

To the best of our knowledge, it is the first study that will evaluate the differences in psychophysiological reactions of internet users exposed to or not exposed to disinformation. Given the proposed hypothesis, we expect that individuals exposed to fluoride-related disinformation will present more psychophysiological reactions during the experiments because of stressors provided by the consumption of novel content. Additionally, those who disagree with the content due to previous health beliefs tend to show more psychophysiological reactions, also considering the cognitive dissonance process [16]. Moreover, it is expected that younger adults with higher levels of eHealth literacy and oral health knowledge probably will feel less persuaded by disinformation than their older counterparts. Finally, we hope to obtain promising results pertaining to the comparison of F_9_ (remote HR) to F_8_ (measured HR), enabling remote validation and measurement of this parameter in future studies on information disorder.

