### Strengths

Although desirable, the mitigation of false or misleading messages from computational detection measures that screen and remove posts on social media does not seem to be enough to end the consumption and spread of digital falsehoods [42]. Indeed, the overload of information on internet channels makes data screening difficult because existing artificial intelligence–based systems cannot cover all health issues [11,43]. Considering this scenario, the proposed methodology is advantageous because it investigates the information disorder phenomenon in terms of the users' reactions, instead of only analyzing it from a content perspective. Furthermore, it is possible to validate the collection of HR data from psychophysiological facial reactions using neural network modeling, which would enable remote monitoring of users through an ordinary camera using a computer [31]. Thus, people would have an additional tool to avoid consuming disinformation.

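### ROC analysis cannot show whether remote heart rate (F9) agrees with measured heart rate (F8) in bpm; the ancillary validation needs an agreement analysis

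*Protocol article*

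**What the plan says.** The analysis paragraph of Data Collection, Management, and Analysis states that "ROC curve analysis will be performed to determine the accuracy of F_9_ concerning F_8". The Trial Design section repeats this: "curve analysis will be performed to determine the accuracy of F_9_ (remote HR) concerning F_8_ (measured HR". So does the abstract: "receiver operating characteristic curve analysis will be performed to determine the accuracy of the remote HR with respect to the measured HR". No other method is named for this comparison.

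Table 2 describes F8 as "Measurement of HR using Polar Ignite 2 and Polar Verity Sense" and F9 as "Estimated measurement of HR using the rPPG^c^ technique". The Intervention section gives the sampling of F8: "To monitor the HR (1 Hz), the participants will be asked to wear 2 digital sports watches". Both are therefore numeric heart rates, and F8 is a series of repeated values within each participant.

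The purpose appears in the Discussion. Under Principal Findings the authors hope for good results from the F9 to F8 comparison, "enabling remote validation and measurement of this parameter in future studies on information disorder". Under Strengths they add that "it is possible to validate the collection of HR data from psychophysiological facial reactions using neural network modeling".

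**The concern.** ROC analysis describes how well a score separates two states. Here the reference is a number, and the question is whether a second instrument returns the same number. These are different properties. Even if F8 is cut in two, the AUC records only whether people or moments with a high F8 tend to have a higher F9 than those with a low F8. It does not record how many bpm separate the two readings.

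This is not a detail that an article leaves to a fuller plan. The article names the method three times, and the method does not answer the question put to it. A cut-off supplied elsewhere would make the ROC analysis feasible, but the AUC would still be based on ranks. At stake is the conclusion about remote heart rate: a high AUC could be reported as accuracy when the analysis holds no information on bias or error in bpm.

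**Working it through.** The article gives no AUC, cut-off or tolerance for this comparison, so there is no figure to reproduce. The check is of what an AUC can detect.

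**Assumptions (none is in the article).** F8 is normal with mean 75 bpm and between-person SD s = 5, 10 or 15. F9 = F8 + random error with SD e = 5 bpm. The cut-off on F8 is 75 bpm unless stated otherwise. One pair of values per participant is used for simplicity.

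**1. Invariance.** AUC = P(F9 of a random pair member with F8 above the cut > F9 of one with F8 below it). Replace F9 by a + b·F9 with b > 0. The inequality a + b·x > a + b·y holds exactly when x > y, so the AUC is unchanged for every a, every positive b and every cut-off on F8.

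**2. Size of the AUC.** With the cut at the mean of F8, the normal orthant formula gives AUC = 1/2 + (2/π)·arcsin(ρ/√2), where ρ = s/√(s² + e²).

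| s (bpm) | ρ | AUC at 75 bpm |
|---|---|---|
| 5 | 5/√50 = 0.707 | 0.83 |
| 10 | 10/√125 = 0.894 | 0.94 |
| 15 | 15/√250 = 0.949 | 0.97 |

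The error of F9 is the same in all three rows. Only the spread of heart rates differs.

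**3. Same AUC, different agreement (s = 10, e = 5).** Limits of agreement are mean difference ± 1.96·5 = ± 9.8 bpm.

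| Remote HR | AUC at 75 bpm | Mean difference (bpm) | 95% limits (bpm) | Mean absolute error (bpm) |
|---|---|---|---|---|
| F9 | 0.936 | 0 | −9.8 to +9.8 | 5·√(2/π) = 4.0 |
| F9 + 15 | 0.936 | +15 | +5.2 to +24.8 | 15.0 |

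A scale fault behaves the same way. For 0.5·F9 + 15 the mean difference is 0.5·75 + 15 − 75 = −22.5 bpm, and the AUC is again 0.936. Simulation confirmed that the AUC was identical under both changes at cut-offs of 60, 70, 75, 80 and 90 bpm.

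**4. Dependence on the cut-off (simulation, same F9).** With s = 10 the AUC is 0.97 at 60 bpm, 0.94 at 75 and 0.97 at 90. With s = 5 it is 0.97, 0.83 and 0.97.

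**5. The significance rule does not help.** The article sets P<.05 for all analyses. For an AUC the usual null value is 0.5, so a significant result shows only that F9 is related to F8. With 52 completers (58 × 0.9 = 52.2), s = 10 and a median cut, a rank test was significant in over 99% of simulated trials at error SD 10 bpm, and in about 73% at error SD 20 bpm.

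**The case against.** Several points on the other side stand and limit the concern.

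- **The comparison is ancillary.** The Outcomes section does not list F9 against F8 separately, and the hypothesis concerns group differences. Watch heart rate is measured independently of F9. A reader might infer that the trial's main comparison is compromised; the article does not support that.
- **No certification rule exists.** The Discussion speaks of hoped-for results and of what is possible. A reader might infer that a given AUC would license dropping the sensor in later studies. The article sets no AUC target and does not say so. The 15 bpm offset is an illustration, not a figure from the article.
- **Descriptive statistics are planned.** Means of F8 and F9 side by side would probably expose a gross uniform shift. They are not the prescribed accuracy analysis, carry no tolerance and do not show error within a person.
- **A sensible cut-off may exist.** It would be too strong to say that none is natural. The design has a 150-second baseline, so heart rate above a participant's own baseline is a candidate state, and the cut-off may be given elsewhere. For change from baseline a constant offset cancels; a scale error does not. The AUC would still carry no information in bpm.
- **Dichotomising F9 at F8's own cut-off would reveal bias.** With s = 10, e = 5 and a cut of 75 bpm, adding 15 bpm lowers specificity from 0.85 to 0.18. That is classification at one fixed threshold, not the ROC curve analysis that is stated.
- **The invariance has limits.** It holds for offsets and positive rescalings common to all participants. Person-specific offsets do change a pooled AUC.
- **Dependence on spread is not unique to the AUC.** At s = 5, 10 and 15 the concordance coefficient, s²/(s² + e²/2), is 0.67, 0.89 and 0.95. Limits of agreement in bpm do not share this weakness under constant error.

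**Conclusion.** The concern holds for the heart-rate validation and should be fixed. As written, the only accuracy analysis for F9 cannot detect a common offset or scale error of any size. Its value also moves with the spread of heart rates in the sample (0.83 to 0.97 over the assumed range at unchanged error) and with the cut-off on F8. It cannot support a conclusion that remote heart rate is accurate in bpm.

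The invariance is exact and needs no distributional assumption. The particular AUC values rest on the assumed normal heart rates and error SD. The randomized comparisons of watch heart rate, facial features and questionnaire answers do not depend on this analysis.

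**What to change.** In the abstract, the Trial Design section and the analysis paragraph, replace ROC analysis with paired agreement of F8 and F9:

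- Average both over fixed, matched windows, for example each 15-second message.
- Report mean bias and 95% limits of agreement by a method that allows for repeated measures per participant, plus mean absolute error in bpm.
- State the acceptable tolerance in bpm before F9 is compared with F8. Agreement does not depend on allocation, so keeping the analysts blind to group is not the relevant safeguard.
- If a concordance coefficient is added, note that it depends on the spread of the sample.
- Keep ROC only as a supplement, and only if a binary state is defined from F8 in advance, such as heart rate above the participant's own baseline.

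The cost is a change of wording in three places and a little more analysis. No further data are needed.

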### Monitoring

#### Data Monitoring

The authors will assume responsibility for independent regulation of data collection, management, and analysis.

#### Hazards

People can feel confused about the trustworthiness of the consumed content and consequently develop negative oral health beliefs. Thus, after the intervention, the trained examiner will clarify all aspects of the information and disinformation for each individual. In this way, they will resolve the doubts and possible misunderstandings regarding fluoride consumption, whether in terms of oral hygiene or drinking water. As a result, the present study also serves as a health education measure for the participants.

### Ethics and Dissemination

#### Research Ethics Approval

This study was reviewed and approved by the Council on Ethics in Human Research from the Bauru School of Dentistry (CAAE: 53483821.0.0000.5417), registered in the Brazilian Clinical Trials Registry (RBR-7q4ymr2) and assigned with the universal trial number U1111-1263-8227.

#### Consent and Assent

Informed consent will be provided and assigned by the participants.

#### Confidentiality

Identification numbers will be used to ensure participant confidentiality during data analysis.

#### Availability of Data

All raw data will be available in an open repository.

#### Ancillary and Posttrial Care

This study is also intended to serve as an oral health education strategy. Thus, participants in the test group will be informed about the falsehood provided, aiming to avoid the development of negative health beliefs. Moreover, all questions about the content consumed will be clarified for all the participants. In addition, participants are expected to observe how disinformation can be harmful in managing their health.

#### Dissemination Policy

The findings will be reported in high-impact dental or medical informatics journals.

## Results

From June 2022, parents and caregivers who frequent the Clinics of Pediatric Dentistry at the Bauru School of Dentistry will be invited to participate in the study and will be randomized into 1 of 2 groups (control or intervention). Data collection is expected to be completed in December 2023. Subsequently, the authors will analyze the data and publish the findings of the clinical trial by June 2024.

## Discussion

### Principal Findings

To the best of our knowledge, it is the first study that will evaluate the differences in psychophysiological reactions of internet users exposed to or not exposed to disinformation. Given the proposed hypothesis, we expect that individuals exposed to fluoride-related disinformation will present more psychophysiological reactions during the experiments because of stressors provided by the consumption of novel content. Additionally, those who disagree with the content due to previous health beliefs tend to show more psychophysiological reactions, also considering the cognitive dissonance process [16]. Moreover, it is expected that younger adults with higher levels of eHealth literacy and oral health knowledge probably will feel less persuaded by disinformation than their older counterparts. Finally, we hope to obtain promising results pertaining to the comparison of F_9_ (remote HR) to F_8_ (measured HR), enabling remote validation and measurement of this parameter in future studies on information disorder.

### Comparison to Prior Work

Notably, the proposed analysis proved effective in detecting remote emotions in experiments with games [31], but it is still necessary to understand its strengths and limitations in the information disorder context. Nevertheless, it could be a precursor to developing artificial intelligence models to detect false health content automatically and prevent consumption in digital environments. In addition, the results can help people who are more susceptible to believe in fluoride-related false messages found on the internet better understand such information.

Furthermore, the present methodology adds a new perspective to the study of information disorder. Currently, this research field focuses on internet-based surveillance of falsehoods on social media to formulate public health measures and policies [24,36,37], besides proposing definitions and taxonomies for a better understanding of this phenomenon [17,38,39]. In this context, previous studies have detected the high prevalence of false or misleading fluoride-related content on distinct social networks [7,24,40,41]. On the other hand, investigations about disinformation concerning the user perspective are still lacking.

